**7. METHODS OF DATA COLLECTION**

The parameters that are collected and documented during the respective study visits are already described in Chapter 6.

7.1 Safety parameters

Adverse events:

Definition see 8.1.1

Adverse events are queried each time the investigator and trial subject come into contact with each other.

7.2 Efficacy parameters

7.2.1 Technical success of the intervention

Defined by the successful implantation of the metal stent at the respective examination-dependent position

In PTBD:

trans stenotic metal stent implantation, verified by the successful outflow of the contrast medium via the metal stent into the distal intestinal segment (imaging: radiological fluoroscopy; this is not study related)

In EUS-AD:

trans stenotic metal stent implantation, verified by the successful outflow of the contrast medium via the metal stent into the distal intestinal segment (imaging: radiological fluoroscopy; this is not study related)

In EUS-HD:

Metal stent implantation transhepatic, verified by the successful outflow of the contrast medium via the metal stent into the intrahepatic dilated bile ducts (imaging: radiological fluoroscopy; this is not study related)

In EUS-CD:

Metal stent implantation transduodenal into the common bile duct, verified by the successful outflow of the contrast medium via the metal stent into the dilated common bile duct (imaging: radiological fluoroscopy; this is not study related)

7.2.2 Clinical success of the intervention

Defined as a drop in bilirubin value in mg/dl ≥ 50% 7 days after completed intervention in relation to the baseline value before intervention

7.2.3 Overall survival

Defined as the time from the beginning of the intervention until death, for whatever reason. If there is no more contact with the patient ("lost to follow up") or the patient is still alive after 6 months, the overall survival is censored to the last contact.

7.2.4 Disease Specific Survival

Defined as the time from the beginning of the intervention until death caused by the underlying malignant disease. If there is no more contact with the patient ("lost to follow up") or the patient is still alive after 6 months, the overall survival is censored to the last contact.

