7. Overall survival (overall survival including any cause of death) and disease specific survival (overall survival which only includes the underlying malignant disease that led to bile duct obstruction)

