5.6 Pre- and concomitant diseases

Pre- and concomitant diseases besides the underlying malignant disease that are present at the time of informed consent are not documented, as they are not expected to have a relevant impact on key endpoints of the study such as the technical and/or clinical success rate or the occurrence of complications of the intervention. By differentiating between Overall Survival and Disease Specific Survival, it is possible to specify the proportion of disease-specific causes (related to the underlying malignant disease causing the biliary obstruction) in the death of patients. It is expected that the underlying malignant disease is the main life-limiting factor in the observation period.

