Serious adverse events (SUE) since intervention (yes/no)

Control visit no.2 (7 days after technically successful intervention

Intensity of pain on the visual analogue scale (0-10) Date Bilirubin determination (after initial intervention)

Laboratory chemical result of the bilirubin determination (after initial intervention, in mg/dl)

Duration of hospital stay from day of intervention (inclusive) to day of discharge (date of hospital discharge, if later than 7 days, please add later!)

Re-intervention(s) since control visit 1 (yes/no) Complication(s) since control visit 1 (yes/no)

Serious adverse events (SUE) since intervention (yes/no)

Control visit no.3 (6 months after intervention) and/or study completion visit

The final study visit coincides with the follow-up visit after six months. To calculate the Overall Survival or Disease Specific Survival, it is noted whether the patient is still alive or when he/she died and why (date of death, calculation of survival time in days, cause of death). If the patient is not examined at the trial centre or has died in the meantime, it must be ensured that the relevant data on re-intervention, adverse events, date of death and cause of death can be obtained by calling the family doctor or relatives.

Data that are documented within the framework of the study:

Date of end of study/last contact

Reason for termination:

- Regular termination of the study (yes/no)

- Patient has died (yes/no)

Date of death

Cause of death on the ground of the underlying malignant disease (yes/no)

Cause of death other than underlying malignant disease (yes/no)

Cause of death unclear (yes/no)

Revocation of consent (yes/no)

Patient no longer appeared/follow-up data no longer to be collected (yes/no)

Intervention not successful, no new attempt

Other (specification)

Chemotherapy carried out during the course (yes/no)

Chemotherapy protocol (name): first line/second line/third line (multiple answers possible)

- Gemcitabine mono (yes/no)

- Gemcitabine/Nab-paclitaxel (yes/no)

- FOLFIRINOX (yes/no)

- Cisplatin/Gemcitabine (yes/no)

- FLO (T) (yes/no)

- FOLFIRI (yes/no)

- Paclitaxel/Ramucirumab (yes/no)

- Ramucirumab mono (yes/no)

- 5 FU mono (yes/no)

- Other chemotherapy/immunotherapy (yes/no)

Other therapy (but no chemotherapy) performed (yes/no)

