The evaluation of further secondary endpoints is done in the ITT set. With regard to the complication rate, PTCD is expected to have a lower complication rate than EUCD. No missing values are implanted during the evaluation of secondary endpoints. The evaluation is purely descriptive. Appropriate statistical methods are used according to the underlying distribution. For continuous endpoints, the mean, standard deviation, median, interquartile distance, and minimum and maximum are reported separately and in total for the two groups. For categorical endpoints, absolute and relative frequencies are given, also separately for the two groups and in total. Event times are displayed and evaluated using survival time analysis methods (e.g. Kaplan Meier). Descriptive p-values are given together with 95% confidence intervals. In the EUCD group, descriptive p-values are also divided by method (see 5.1). In addition, unless defined in the secondary endpoints, adverse events are evaluated and compared.

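### Disease-specific survival gives deaths from other or unclear causes no status; under Kaplan-Meier they would be censored and the 6-month risk of tumour death modestly overstated

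*Protocol*

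**What the plan says.** Three parts of the protocol bear on this.

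- **Event.** Section 7.2.4 reads "Defined as the time from the beginning of the intervention until death caused by the underlying malignant disease". The endpoint list in section 2 agrees: "disease specific survival (overall survival which only includes the underlying malignant disease that led to bile duct obstruction".
- **Censoring.** Section 7.2.4 goes on to cover patients with whom contact is lost, or where "the patient is still alive after 6 months, the overall survival is censored to the last contact". It names overall survival, not disease-specific survival. The same rule stands in section 7.2.3, where the event is different: "Defined as the time from the beginning of the intervention until death, for whatever reason".
- **Analysis.** Section 9.2 says "Event times are displayed and evaluated using survival time analysis methods (e.g. Kaplan Meier", adds descriptive p-values and 95% confidence intervals, and says of the secondary endpoints "The evaluation is purely descriptive".

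Section 6.4 (control visit no. 3) records the date of death and three categories of cause: the underlying malignancy, another cause, and "Cause of death unclear (yes/no". Section 5.6 says that separating the two survival endpoints means "it is possible to specify the proportion of disease-specific causes" of death.

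**The concern.** For overall survival the two censoring states are complete, because every death is an event. Once the event is narrowed to tumour death, a third outcome exists: death from something else, or from a cause nobody could establish. The sentence in section 7.2.4 was not adapted to that, so such a patient is neither an event nor in either censoring state.

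An analyst who keeps the stated event and uses the named method would censor these patients at death. Kaplan-Meier then treats them as if they could still die of the tumour later. The resulting curve estimates tumour mortality in a hypothetical setting without other deaths, and it lies above the proportion of patients who actually die of the tumour. A reader would probably take it for that proportion. If other-cause deaths are commoner in one arm, the two curves are overstated by different amounts.

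**Working it through.** **Plan figures.** The protocol states no figure for disease-specific survival. The only number needed from it is 106 patients per arm (sections 4.1 and 9.1). That number reproduces: the Farrington-Manning formula gives 99.4, so 100 per arm, and 100/0.95 = 105.3, so 106.

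**Assumptions (not in the protocol).** Net 6-month tumour mortality *m* of 50% or 60%. A fraction *q* of patients, 2%, 5% or 10%, with an early death from another cause, independent of the tumour death time. Six months is taken as 182.5 days.

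**Formulas.** With other-cause deaths censored and independent, one minus Kaplan-Meier (1-KM) estimates *m*. The cumulative incidence (CIF) of tumour death is:

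- other-cause deaths at about day 0: CIF = *m*(1 − *q*), so the excess is *qm*;
- other-cause deaths spread evenly over days 0-30: CIF = *m*(1 − *q*) + *qF*. Here *F* is the mean probability of having already died of the tumour by then. With exponential tumour death times, *F* = 0.055 for *m* = 50% and 0.072 for *m* = 60%.

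Example: *m* = 60%, *q* = 10%. At day 0, 0.60 × 0.90 = 54.0%. Spread, 0.54 + 0.10 × 0.072 = 54.7%. 1-KM gives 60%.

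| *m* (1-KM) | *q* | CIF, day 0 | CIF, days 0-30 | Excess (points) |
| --- | --- | --- | --- | --- |
| 50% | 2% | 49.0% | 49.1% | 0.9-1.0 |
| 50% | 5% | 47.5% | 47.8% | 2.2-2.5 |
| 50% | 10% | 45.0% | 45.5% | 4.5-5.0 |
| 60% | 2% | 58.8% | 58.9% | 1.1-1.2 |
| 60% | 5% | 57.0% | 57.4% | 2.6-3.0 |
| 60% | 10% | 54.0% | 54.7% | 5.3-6.0 |

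The standard error of one arm's estimate is √(CIF(1 − CIF)/106). At 54.7% this is √(0.547 × 0.453/106) = 4.8 points. The excess is therefore about 0.2 standard errors at 2%, about half at 5%, and about one at 10%.

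**Second pattern.** If both causes act at constant hazards, all-cause mortality is *M* and a share *s* of deaths is non-tumour, then CIF = *M*(1 − *s*) and 1-KM = 1 − (1 − *M*)^(1−*s*). With *M* = 60%: *s* = 10% gives 54.0% against 56.2%, and *s* = 20% gives 48.0% against 52.0%. The direction is the same and the size similar.

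**Additivity.** Take *m* = 60% and *q* = 10% at day 0. All-cause mortality is 0.10 + 0.90 × 0.60 = 64%. The cumulative incidences add up to it: 54 + 10 = 64. The 1-KM values do not: 60 + 10 = 70. The tumour's share of deaths is 54/64 = 84%; reading it from the 1-KM curve would give 60/64 = 94%.

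**Between arms.** With equal *m* = 60% and early other-cause deaths of 5% in one arm and 10% in the other, the 1-KM curves coincide while the cumulative incidences differ by 57.0 − 54.0 = 3.0 points. The standard error of that difference is about 6.8 points, so the shift is under half a standard error. With equal *q* and equal *m* the bias cancels. With equal *q* and different *m*, the difference is only stretched by 1/(1 − *q*), for example 10.0 against 9.5 points for 60% and 50% at *q* = 5%.

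**The case against.** The strongest reply is that the protocol does not prescribe the faulty analysis. Kaplan-Meier is given as an example, cumulative incidence is itself a survival-time method, section 7.2.4 never says that other-cause deaths are censored, and section 9 leaves detail to an SAP that is not at hand. This stands in part: the censoring is an inference. But which deaths are events is part of the endpoint definition, section 7.2.4 sets that definition out, and its censoring sentence names the wrong endpoint.

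A reader might infer that procedure deaths are hidden in this trial. The documents do not support that. They count in overall survival (section 7.2.3). Within 30 days they count in the complication endpoint, which expressly includes death (section 2) and is the one secondary endpoint tested in the hierarchy (section 9.2). They are also graded as fatal complications (section 8.1) and reported as serious adverse events (section 8.4). They drop out only of the disease-specific curve.

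A reader might also infer that section 5.6 cannot be met. It can: the share of deaths due to the tumour is a ratio of CRF counts. Only reading that share from the Kaplan-Meier curve would mislead.

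Finally, the larger scenarios are stretched if the competing deaths are mainly procedural. Section 9.2 expects complications in 10-20% of patients, so 10% procedure deaths would need half to all of them to be fatal. Section 5.6 expects the tumour to be the main life-limiting factor. The 30-day mortality of up to 33% in section 1.1 is not split by cause and cannot serve as an estimate of non-tumour deaths. These objections limit the size, not the direction.

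**Conclusion.** The point holds as a minor one and is best treated as a cheap improvement. The censoring sentence in section 7.2.4 is wrong as written and leaves deaths from other and unclear causes undefined. If they are censored under Kaplan-Meier, the 6-month probability of tumour death is overstated by about 1 point with 2% early other-cause deaths, 2 to 3 points with 5%, and 4 to 6 points with 10%. These figures rest on an assumed net tumour mortality of 50-60% and on independence of the two causes. The protocol's own expectations point towards the lower end.

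The comparison of arms is materially affected only if other-cause death rates differ between them. The endpoint is secondary and descriptive, so the non-inferiority test, the hierarchy and the sample size are untouched.

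**What to change.** - **Section 7.2.4:** make the censoring sentence refer to disease-specific survival, and define death from a cause other than the underlying malignancy as a competing event.
- **Section 9.2:** report by arm the cumulative incidence of tumour death and of other-cause death (Aalen-Johansen), next to overall survival.
- **Unclear causes:** add a sensitivity analysis that scores these deaths first as tumour deaths and then as competing deaths.

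A cause-specific log-rank p-value may stay as a descriptive comparison. Gray's test is optional; it answers a different question, since more other-cause deaths in an arm lower that arm's incidence of tumour death.

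The cost is a few sentences and one extra standard analysis. Date and cause of death are already on the CRF (section 6.4), so no new data are needed.

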**8. ASSESSMENT OF PATIENT SAFETY**

8.1 Definition and documentation of complications

In the study population with advanced oncological diseases, numerous tumour- and tumour therapy-related adverse events are to be expected.

For the assessment of patient safety with regard to the interventions performed in the study, only certain adverse events in terms of potential complications of PTBD/EUCD, of which a major part is to be expected within a period of 30 days after the intervention, are of interest and complications are to be documented in the notification form.

The following potential complications of PTBD and/or EUCD are recorded in the CRF with date and severity (mild, moderate, severe, fatal) (see Table 1, below) (multiple entries possible):

- Bleeding/haematoma

- Haemobilia

- intra-abdominal bile leakage

- Pneumothorax

- Biliary pleural effusion

- Pneumoperitoneum

- Perforation of the gastrointestinal tract

- Therapy-relevant (cholangial-)sepsis

- Newly occurring cholangitis (see comment below)

- Abscess

- Purulent peritonitis

- Cholecystitis

- Metal stent dysfunction/migration

- Other (description in free text)

To be distinguished from the above mentioned complications and not to be recorded:

- metal stent-closure caused by the ingrowth of tumour tissue or by choledocholithiasis

- Adverse events associated with anaesthesia and/or sedation

- Adverse events associated with chemotherapy

- Cholangitis as a possible complication of the intervention by PTBD or EUCD requires a special consideration: Only the newly appeared and not the pre-existing cholangitis is considered a complication ! Since the patients are treated peri-procedurally prophylactically with antibiotics, cholangitis is only considered a complication if an intensification of antibiotic therapy becomes necessary and the cholangitis can be safely attributed to the intervention !

- Postinterventional pain (will be collected separately)

Severity of the complication

Table 1: Severity of complications according to the recommendations of the American Society for Gastrointestinal Endoscopy (ASGE) (16,17)

| **Severity of the complication** | **Slightly** | **Moderate** | **Severe** | **Fatal** |
| --- | --- | --- | --- | --- |
| Procedure aborted or not yet started because of UE | x |  |  |  |
| Unscheduled anesthesiological measure required in connection with a procedural adverse event (e.g. endotracheal intubation) |  | x |  |  |
| Unplanned return to hospital or extended hospital stay: ≤ 3 days | x |  |  |  |
| Unscheduled return to hospital or extended hospital stay: 4-10 days |  | x |  |  |
| Unscheduled return to hospital or extended hospital stay: > 10 days |  |  | x |  |
| Unplanned stay intensive care unit: ≤ 1 night |  | x |  |  |
| Unplanned stay intensive care unit: > 1 night |  |  | x |  |
| Blood transfusion necessary (EK) |  | x |  |  |
| Additional endoscopic examination necessary (e.g. hemostasis) |  | x |  |  |
| Additional radiological intervention necessary (e.g. coiling) |  | x |  |  |
| Surgical intervention necessary |  |  | x |  |
| Permanent damage/permanent disability remains |  |  | x |  |
| Death |  |  |  | x |

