**2. OBJECTIVES AND ENDPOINTS**

Primary objective and primary endpoint

The primary objective of the study is to show that PTBD is not inferior to EUCD in terms of technical success rate. The technical success rate is defined as the successful implantation of a metal stent into the bile duct system (= successful drainage of the contrast medium via the metal stent within one minute after injection).

The primarily technical success of the intervention is decisive for the further procedure following the examination (reintervention necessary ? surgery necessary ?) and is presumably almost identical to the clinical success of the intervention, which can only be verified after 7 days (drop in bilirubin value ≥ 50%). The technical success rate was therefore preferred to the clinical success rate as the primary endpoint.

In PTBD there is only one possibility of metal stenosis insertion across the tumor stenosis in the common bile duct (blunt). In EUCD, the additional option of transluminal stent placement in the context of EUS-HGS or EUS-CDS remains.

The prompt (1 week) implantation of a metal stent after the application of an external drainage in PTBD is also considered a technical success. However, the application of an external drainage is counted as "reinvention".

Secondary objectives and secondary endpoints

In addition to the technical success rate, both interventions will be compared descriptively with regard to other endpoints. All endpoints or points in time refer to the technically successful intervention.

1. Clinical success rate of bile extraction, defined as reduction of the bilirubin value of ≥ 50% 7 days after technically successful intervention in relation to the baseline value before intervention.

2. The occurrence of at least one complication (including death) within 30 days (description + count)

3. Duration of bile duct intervention (PTBD/EUCD) in minutes

- for PTBD: from the application of the local anaesthetic to the application of the skin dressing

- for the EUCD: from the insertion of the endoscope to the removal of the endoscope

4. Post-interventional pain sensation on day 1 and day 7 after intervention (in relation to baseline before intervention): visual analogue scale

5. Length of hospital stay (from the day of the first intervention to the day of discharge) in days

6. Number of re-interventions between the first intervention and the end of the follow-up

(n) after 6 months.

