**5. TREATMENTS/ INTERVENTIONS**

5.1 Description of the treatment(s)/ intervention(s)

PTBD

PTBD is performed in the first step by means of (colour contrast Doppler) ultrasound-guided puncture of an (dilated) intrahepatic bile duct using an access needle (e.g. Chiba needle (22G/0.7mm diameter). In the next step, the application of contrast medium into the bile duct system is performed under radiological fluoroscopy. The access route should be at a sufficient safety distance from neighbouring structures, i.e. the pleura in case of right-sided access.

Ideally, after KM filling of the bile duct system, a wire should be advanced distally beyond the stenosis in the common bile duct. This can also be done after changing to a larger wire (from 0.018" to 0.035"). After placement of an appropriate guide wire, a corresponding metal stenosis implantation (SEMS) should be performed in the same session in the area of the stenosis of the common bile duct (usually 8 or 10 mm diameter with different lengths (usually 6 -10 cm).

For further precision, the release of the metal stent can (not obligatory) be controlled by an additional luminal endoscopic visualization. (usually in relation to the papilla or the protrusion into the duodenum). This is particularly relevant with regard to endoscopic reintervention. Even in cases of tumour-related duodenal stenosis (use of a thinner endoscope) or altered anatomy after abdominal surgery (e.g. access via the feeding loop after Billroth II surgery). it is very often possible to reach the papilla (e.g. using a gastroscope).

Leaving a percutaneous plastic drainage after successful implantation of a metal stent should be avoided (counted as reintervention). If metal stent implantation is not possible in the initial PTBD, an internal/external plastic drainage should be inserted and the sole external drainage should be avoided (highest risk of complications).

EUCD

Endosonographically controlled cholangiodrainage (EUCD) is performed according to the current state of knowledge of this technique (2-9,14,15).

The choice of the respective EUCD method depends on the examiner. First and foremost, however, an antegrade stenting in the sense of an EUS-AD (wire is passed over the stenosis) should be performed.

should be attempted, since - in contrast to the transluminal procedure - the original anatomy of the bile duct system is preserved and the least complications are expected.

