6.2 Baseline visit

Facts of the clinical picture are documented (Case Report Form,p.3) . Cause of malignant bile duct obstruction, date of first diagnosis of the malignant underlying disease, cause of unsuccessful or for anatomical reasons not feasible ERCP.

The bilirubin value in mg/dl as an expression of the bile duct obstruction or cholestasis is measured and noted. The baseline visit should be performed the day before the intervention. Depending on the timing within the centre, baseline visit can be on the same day as screening visit if the intervention is scheduled for the following day.

Data that are documented as part of the study:

Demographics

- Gender

- Age

- Size

- Weight

Cause of the malignant bile duct obstruction (no multiple answers)

- Pancreatic carcinoma

- Distal bile duct carcinoma or extrahepatic bile duct carcinoma (Bismuth I)

- Gall bladder carcinoma

- Stomach cancer

- Duodenal carcinoma

- Papillary carcinoma

- Metastasis of another malign disease

- Other cause

Date of first diagnosis of the underlying malignant disease

Cause of unsuccessful or for anatomical reasons not feasible ERCP (no multiple answers)

- Gastric outlet stenosis/duodenal stenosis (tumour-related or benign cause)

- Difficult to probe the optic disc using ERCP

- For (partial) gastrectomy

- Biliodigestive anastomosis

- Following bariatric surgery

- Other cause

Laboratory chemical result of bilirubin determination (in g/dl) Pain intensity on the visual analogue scale (0-10)

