9.2 Statistical evaluation

The primary endpoint is the technical success rate in malignant distal choledochial stenosis using a self-expanding metal stent. The non-inferiority of PTBD compared to EUCD shall be demonstrated. The corresponding test hypothesis is

H0: pEUCD - pPTBD ≥ δ vs. H1: pEUCD - pPTBD < δ

Where pPTBD describes the technical success rate in the EUCD group, pPTBD the technical success rate in the PTBD group and δ=0.1 the non-inferiority limit.

The non-inferiority of PTBD to EUCD is verified by the Farrington/Manning test with a one-sided significance level of 2.5%.

Since this is a non-inferiority study, the primary evaluation will be based on both the Intention-To-Treat (ITT) Set and the Per-Protocol (PP) Set. In the ITT set, all patients are considered in whom the intervention was performed, even if it was technically unsuccessful or participation in the study was terminated prematurely. If the intervention has to be terminated prematurely (e.g. due to organ perforation), this patient is included in the primary evaluation. The primary evaluation is based on the assumption of technical failure in these patients.

In the PP Set, only those patients are included in the evaluation for whom the intervention was performed and the technical success was measured.

In sensitivity analyses, best case and worst case scenarios are calculated for the missing values. In addition, regression models are planned to investigate the influence of confounders on the endpoints. The variables intervention (EUCD with subgroups or PTBD with side localisation), BMI or bilirubin value are considered as input variables in the baseline study. The binary outcome variable is the technical success of the intervention. The affiliation of the individual patients to the two evaluation collectives is defined in SAP before the database is closed.

If non-inferiority can be shown with regard to the technical success rate, the occurrence of at least one complication (expected complication rate for both interventions: 10-20%) is compared hierarchically in the next step and tested for differences between the groups (based on the ITT set). Due to the hierarchical approach, the full level alpha, in this case two-sided 5%, is tested.

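### Anaesthesia and sedation events are barred from the complication record behind the hierarchical complication test, an omission that may fall unequally on the two arms and could be neither seen nor adjusted for

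*Protocol*

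**What the plan says.** Protocol section 8.1 gives a checklist of complications for the CRF, followed by a second list headed "To be distinguished from the above mentioned complications and not to be recorded". One entry on that second list is "Adverse events associated with anaesthesia and/or sedation". The rule is worded identically for both arms.

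The record feeds secondary endpoint 2 in section 2: "The occurrence of at least one complication (including death) within 30 days". Section 2 calls the secondary comparisons descriptive, but section 9.2 gives this endpoint a confirmatory role. Once non-inferiority is shown, it "is compared hierarchically in the next step and tested for differences between the groups (based on the ITT set"), at the full two-sided 5%. The expected rate is 10-20% in both arms.

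On exposure, section 2 times EUCD from insertion to removal of the endoscope, so every EUCD is endoscopic. It times PTBD differently: "for PTBD: from the application of the local anaesthetic to the application of the skin dressing". Section 5.1 says that stent release in PTBD "can (not obligatory) be controlled by an additional luminal endoscopic visualization". Section 4.2 confines each centre to one technique. The intervention-day data in section 6.3 include no sedation or anaesthesia type.

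**The concern.** A rule applied alike to both arms is neutral only if both arms are exposed alike to what it removes. The protocol neither ensures nor measures that. Because each centre contributes to one arm only, local sedation practice is wholly confounded with treatment. Without a sedation field on the CRF, a difference could be neither described nor adjusted for.

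Section 1.2 says that complication rates are to help decide which method should be preferred after ERCP. If sedation or airway events are commoner in EUCD, leaving them out makes EUCD look safer relative to PTBD than it is, in the only safety comparison tested at full alpha. The SAP cannot repair this, because an analysis cannot restore events that were never recorded.

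**Working it through.** **1. The plan's own figure.** The only related figure in the protocol is the sample size in section 9.1. Take success of 0.95 in both arms, a margin of 0.10 and one-sided 2.5%. The restricted estimates under the null are then 0.9703 and 0.8703.

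- s0 = √(0.9703×0.0297 + 0.8703×0.1297) = 0.3764
- s1 = √(2×0.95×0.05) = 0.3082
- n = [(1.960×0.3764 + 0.8416×0.3082)/0.10]² = 99.4, so 100 per group
- 100/0.95 = 105.3, so 106 per group

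The stated size is reproduced. It does not bear on the present point, except that 106 per arm is the size used in step 3.

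**2. How much the exclusion could hide.** The protocol gives no rate for sedation or anaesthesia events, so the rates below are assumptions. Let b be the rate of all other complications, equal in both arms and taken as 10% to 20% from section 9.2. Let sE and sP be independent sedation-event rates in EUCD and PTBD. The full complication rate in an arm is 1 − (1 − b)(1 − s), so the hidden difference is (1 − b)(sE − sP).

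| Assumed sE / sP | b = 10% | b = 20% |
|---|---|---|
| 2% / 0% | 0.90×2 = 1.8 points | 0.80×2 = 1.6 points |
| 5% / 0% | 4.5 points | 4.0 points |
| 5% / 2.5% | 2.25 points | 2.0 points |
| 10% / 0% | 9.0 points | 8.0 points |
| equal | 0 | 0 |

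The sign follows sE − sP. If PTBD had more such events, the omission would favour PTBD.

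**3. What this means for the test.** Suppose the events were recorded. With 106 per arm, the chance of a significant result showing EUCD worse is Φ[(d − 1.96×SE0)/SE1], with SE0 pooled and SE1 unpooled. With no difference, this chance is 2.5%.

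- 2% / 0%: 6.2% (b = 10%) to 4.7% (b = 20%).
- 5% / 0%: 16.8% to 10.4%. For b = 10%: d = 0.045, SE0 = 0.0450, SE1 = 0.0449, and Φ(−0.963) = 0.168.
- 10% / 0%: 46.0% to 27.5%.

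At the lower assumed rates the effect on the test is small. It becomes material only at rates for which the protocol offers no support.

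**4. The passages side by side.**

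- *Death.* Endpoint 2 includes death within 30 days. Section 8.1 says sedation events are not recorded and makes no exception for fatal ones.
- *Intervention day.* Section 6.3 documents adverse events with a severity grade and does not carve out sedation. Section 8.1 does.
- *Serious adverse events.* Section 4.6.2 covers any adverse event with a listed consequence, whatever its link to the intervention. Section 8.4 uses nearly the same definition but ties it to the serious or fatal complications of 8.1. On that reading, a sedation event with a serious consequence may fall outside reporting.
- *Stopped procedures.* Under section 9.2, a patient whose intervention is terminated prematurely is a technical failure. If sedation was the cause, 8.1 leaves no complication to record.

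**The case against.** The strongest reply is that unequal exposure is inferred, not stated. No section gives a sedation regimen for either arm. Section 6.1 provides an information form on sedation or anaesthesia without separating the arms, which suggests that it is foreseen in both. The local anaesthetic in section 2 only starts the clock for procedure duration. Endoscopic control, although optional in PTBD, is listed in section 1.1 among the aspects of optimal PTBD. All of this stands. A reader might infer that EUCD always carries this risk, that PTBD does not, and that the comparison is therefore tilted. The documents support only that it may be.

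A reader might also infer that gastric outlet or duodenal stenosis makes aspiration a problem of EUCD. Section 6.2 lists that stenosis as a baseline category for both arms, and section 5.1 foresees endoscopic control of PTBD in duodenal stenosis. The documents support no arm-specific aspiration risk.

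Nor does the severity table flatly contradict the exclusion. Its row reads "Unscheduled anesthesiological measure required in connection with a procedural adverse event (e.g. endotracheal intubation"), so it grades the consequence of a procedural event, such as intubation after a bleed. What remains is that no rule tells a site when an intubation is procedural and when it is sedation-related.

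Some events would still surface: date and cause category of death are collected (section 6.4), adverse events are queried at every contact (section 7.1), and a stopped procedure counts against its arm in the primary analysis. It would be too strong to say that every such event is lost. But 8.1 is the specific rule for the complication record, and it may override the general ones.

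Finally, limiting the endpoint to complications of the drainage itself is a legitimate and symmetric scope. That holds as a choice of endpoint. It does not justify leaving uncollected the data that would show whether the choice matters.

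**Conclusion.** The point holds as a possible differential omission in the one safety comparison tested at full alpha, together with passages that need reconciling. A tilt is not established and its size cannot be derived from the protocol. Under assumed event rates of 2% to 5% in EUCD and none in PTBD, independent of other complications, 1.6 to 4.5 points would be hidden. The figure is zero if exposure and event rates are equal, and the sign reverses if PTBD has more events. Even with equal rates, the complication rates of both arms would be somewhat understated and the inconsistencies in step 4 would remain. This is a cheap improvement, not a flaw that invalidates the comparison.

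**What to change.** - In section 8.1, take anaesthesia and sedation events off the list of items not recorded.
- Add one CRF item for peri-procedural cardiopulmonary or airway events, in both arms, graded by the existing severity table.
- Record the type of sedation or anaesthesia with the intervention-day data of section 6.3, in both arms.
- State that every death within 30 days counts in endpoint 2.
- Reconcile sections 4.6.2, 6.3, 8.1 and 8.4 so that it is clear which sedation-related events are documented and which are reported as serious.
- Report the complication comparison with and without the sedation item.

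The cost is two extra CRF items and a few lines of protocol text. The stated complication rate will be slightly higher, and the figure without the item is needed for comparison with earlier series. None of this changes how patients are sedated or treated. It would also let the trial show that the exclusion made no difference, if that proves to be so.
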